#### Quality-of-life and health economic outcome measures

Utility will be measured using the EuroQol (EQ-5D-5 L), deriving quality-adjusted life years (QALYs) for each participant. Disease-specific quality-of-life measures are listed in Table 2.

#### Imaging outcome measures

Gadolinium-enhanced 1.5/3.0 T MRI of the signal knee will be performed at baseline and six months according to the protocol outlined in Table 3. All images will be quality controlled by an experienced musculoskeletal radiologist within two weeks of acquisition to ensure that the image quality is sufficient for scoring purposes. MRIs will be centrally scored semi-quantitatively and quantitatively at the end of the study. Semi-quantitative scoring will be conducted using the MRI Osteoarthritis Knee Score (MOAKS) [51]. Images will be quantitatively scored using statistical shape modelling technology to automatically quantitate total and compartmental synovial volume, total and compartmental bone shape and other relevant features including cartilage morphology [52].

**Table 3 Tab3:** **Magnetic resonance imaging acquisition protocol**

**Plane**	**Sequence**	**Slice Thickness**
Sagittal	T1 SE	2 mm
Sagittal	PD FSE TE = 40 Fat Saturated	3 mm
Sagittal	T2 FSE Fat Saturated	3 mm
Coronal	PD FSE TE = 40 Fat Saturated	3 mm
Coronal	STIR	4 mm
Axial	PD FSE TE = 40 Fat Saturated	3 mm
Post gadolinium:		
Sagittal	T1 3D SPGR Fat Saturated/Water Excitation	Isotropic

### Sample size

The standard deviation used in the sample size calculation is an estimate from previous studies. The internal pilot study will be used to re-estimate the sample size required and increase the recruitment target if necessary.

A data-driven analysis which related change on an NRS with patient global assessment of change using data from 10 similar trials of chronic pain showed that a 30% change, or two points on the NRS was related to change of clinical importance in chronic pain. The correlation between clinician and patient global assessment of change was high in this review, and the large sample size used underscores the external validity of these estimates [53]. This estimate of a two-point change on a NRS being associated with a ‘much better’ improvement was also seen in a prospective cohort of patients with chronic musculoskeletal pain [54].

In a recent placebo-controlled, 121 patient, OA knee trial using an 11-point pain NRS as the primary outcome, the mean (standard deviation (SD)) baseline pain score was 6.1 (2.1) in the control group, 7.7 (1.4) in the placebo group, 7.1 (2.8) in treatment group A and 6.7 (2.5) in treatment group B [55]. In a separate 73 patient OA knee trial, the mean (SD) baseline pain score was 4.0 (2.1) in group A and 4.3 (1.9) in group B. At 12 months, the mean (SD) within-group difference was 0.9 (2.1) for group A and 1.3 (2.4) for group B [56]. For the sample size calculation an SD of 4 is used as a conservative estimate.

The expected consistency in baseline pain among our trial population allows the use of raw change in score, rather than percentage change [53]. In order to detect a two-point change, with an assumed SD of 4 (80% power and 5% significance level), 64 participants per arm are required. Allowing for a conservative 20% dropout rate, a total of 160 participants will therefore need to be recruited into the study.

### Trial procedures

Ethical approval for the study has been granted by the Leeds West Research Ethics Committee (reference number 13/YH/0279). Informed written consent will be obtained from all participants.

### Participant recruitment strategy

Since knee OA is primarily managed within primary care, our recruitment strategy must enable a clear interface between primary care centres and the secondary care sites at which trial activity will take place. Relevant Clinical Commissioning Group (CCG) approvals will be obtained to enable primary care sites to act as Patient Identification Centres (PICs), with potentially eligible patients referred on to local secondary care study teams.

A total of 160 subjects with symptomatic knee OA will be recruited and randomly allocated to either the treatment or placebo control group. Recruitment methods will include advertisements through the local media and community groups, invitations to previous study participants who have given their consent to be contacted regarding future research projects and liaisons with musculoskeletal physicians, general practitioners and allied health professionals. Recruitment will be initiated at all sites as soon as local approvals are in place, therefore recruitment to the pilot phase may occur from multiple sites. There will be no pause in recruitment once 30 patients are recruited, as the outcome from the analysis of the pilot phase will be to either continue to the planned numbers or to increase the planned sample size.

### Informed consent and participant confidentiality

Informed consent will be obtained before patients are screened for participation in the PROMOTE trial. The right of the patient to refuse consent without giving reasons will be respected. Further, the patient will remain free to withdraw from the study at any time without giving reasons and without prejudicing any further treatment. The written consent will be obtained by an appropriately delegated clinician who is, by education and experience, qualified to do so, and who has signed and dated the staff authorization and delegation log. The process of obtaining written consent will be clearly documented in the patient’s medical notes. Patient confidentiality will be guaranteed at all times, in line with the requirements of the United Kingdom Data Protection Act 1998 and NHS regulations.

### Eligibility criteria

Participants must meet the inclusion and exclusion criteria (shown in Table 4) in order to participate. These will be assessed at the screening visit (Figure 2). Potential participants who are deemed ineligible at screening will be allowed a second screening visit if the reason for ineligibility is a temporary status (for example, recent corticosteroid injection; Table 4).

**Table 4 Tab4:** **Eligibility criteria**

**Inclusion criteria**	**Exclusion criteria**
Fulfil clinical ACR Criteria for knee OA	The presence of any inflammatory arthritis (such as gout, reactive arthritis, rheumatoid arthritis, psoriatic arthritis, seronegative spondyloarthropathy, previous diagnosis of pseudogout in target joint with proven crystals on joint aspiration or elevated CRP at time of knee arthritis flare) or fibromyalgia.
Knee pain on most days in the last 3 months	
Knee pain is the predominant pain condition	Use of intra-articular (IA) hyaluronic acid in the signal knee within the 4 months preceding enrolment in the study^a^
Insufficient pain relief from, inability to tolerate or contra-indication to oral and/or topical NSAIDs and/or opioids. Moderate to severe pain of the signal knee as defined by a score of ≥40 mm on a VAS (0 to 100 mm) using the question ‘On average, how would you rate your knee pain during the last 3 months?’.	Use of IA, IM (intra-muscular) or oral corticosteroids in the 3 months preceding enrolment^a^
	Use of other anti-synovial agents (such as hydroxychloroquine or sulphasalazine) in the 2 months preceding the study^a^
	Significant knee injury or any knee surgery within the 6 months preceding enrolment in the study^a^
Patient able to identify a ‘signal’ painful knee (either the most painful knee or selected from equally painful knees)	The presence of non-OA causes of pain in the signal knee, such as referred hip pain, osteonecrosis or radicular spinal pain
A previous radiograph (X-ray) of the signal knee within the last 2 years with changes consistent with tibiofemoral OA	Commencement of physiotherapy or non-pharmacological knee OA treatment in the 2 months preceding the study^a^
No change in the average weekly dose of oral or topical analgesics (including NSAIDs) for at least 4 weeks^a^	A history of partial or complete joint replacement surgery in the signal knee at any time, listed for knee surgery or anticipating knee surgery during the study period
Has used chondroitin or glucosamine for at least 3 months with no change to the average weekly dose, is not using or is willing to stop using if recently started^a^	Women who are pregnant, breast-feeding or men or women planning pregnancy within 18 months after screening (approximately 6 months following last study medications)
All male and female subjects biologically capable of having children must agree to use a reliable method of contraception for the duration of the study and 24 weeks after the end of the study period. Acceptable methods of contraception are surgical sterilisation, oral, implantable or injectable hormonal methods, intrauterine devices or barrier contraceptives.	Use of any investigational (unlicensed) drug within 1 month prior to screening or within 5 half-lives of the investigational agent, whichever is longer^a^
	Have current signs or symptoms of severe, progressive or uncontrolled renal, hepatic, haematological, gastrointestinal, endocrine, pulmonary, cardiac, neurologic or cerebral disease
If female have potential for child bearing then a negative pregnancy test must be performed prior to starting treatment.	Poor tolerability of venepuncture or lack of adequate venous access for required blood sampling during the study period
The patient must be able to adhere to the study visit schedule and other protocol requirements	Uncontrolled disease states, such as moderate or severe asthma, COPD or inflammatory bowel disease, where flares are commonly treated with oral or parenteral corticosteroids, or recurrent infections
The patient must be capable of giving informed consent and the consent must be obtained prior to any screening procedures	Unwilling to keep alcohol intake to below the recommended maximum daily limit during the trial (2 units per day for women, 3 units per day for men)
All patients must have had a chest radiograph (X-ray) within the last 6 months	Planned need for live vaccination during 12 months of study (for example for foreign travel) with exception of Zostavax®, which is permissible
Aged ≥18 years	Melanoma or non-skin cancer in the past 3 years^a^
	Intolerance to lactose
	Significant haematological or biochemical abnormality:
	Haemoglobin ≤8.5 g/dL
	WCC ≤3.5 × 10^9^/L
	Neutrophils ≤1.5 × 10^9^/L
	Platelets ≤100 × 10^9^/L
	ALT >2 times ULN for the laboratory conducting the test.
	Creatinine >1.5 times ULN for the laboratory conducting the tested
	eGFR <30 mL/minute

^a^Criteria for which participants may be rescreened if they are ineligible at the initial screening visit. ALT, alanine aminotransferase; COPD, chronic obstructive pulmonary disease; eGFR, estimated glomerular filtration rate; IA, intra-articular; IM, intramuscular; IV, intravenous; RA, rheumatoid arthritis; ULN, upper limit of normal; VAS, visual analogue scale; WCC, white cell count.

**Figure 2 Fig2:**
[figure not shown]
**Participant flowchart.** EQ-5D, EuroQol 5D-5 L; HADS, hospital anxiety and depression scale; ICOAP, intermittent and constant osteoarthritis pain scale; MRI, magnetic resonance imaging; MTX, methotrexate; NHS, National Health Service; NRS, numerical rating scale; OA QoL, osteoarthritis quality of life; PIS, patient information sheet; SF-12, Short Form-12; WOMAC, Western Ontario and McMaster Osteoarthritis Index. Treatment assignment and allocation concealment.

Identical over-encapsulated MTX and placebo capsules will be produced to ensure allocation concealment. Upon production, study medication will be packed into bulk numbered bottles according to a randomization schedule. This will be prepared by the contract manufacturer using a computerized random number generator, thereby guaranteeing full allocation concealment. Study medication will be issued in numerical order by the pharmacy. Participants in each site will be randomly assigned to the intervention arm or the placebo arm in a ratio of 1:1, and the randomization will be double-blind.

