## Methods/Design

The PROMOTE trial is an investigator-initiated, multi-centre, 160 patient, randomized placebo-controlled trial to compare the reduction in pain associated with knee OA with MTX as compared to placebo. Participants will be randomized on a 1:1 basis to MTX or placebo, and treatment will be for 12 months.

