#### Choice of dosing for methotrexate in patients with osteoarthritis

MTX is currently used in RA with a maximum dose of 25 mg per week. Previous small studies in OA have used lower doses than those used in RA [37,38]; however to alleviate concerns around inefficacy due to inadequate dosing, we will follow current guidelines for use of MTX in RA as the model for the PROMOTE trial. Participants will be prescribed 10 mg MTX or placebo weekly for two weeks, followed by 15 mg weekly for two weeks, 20 mg weekly for two weeks and 25 mg weekly for the remainder of the study if there is no toxicity as determined at the physician’s discretion [43,44]. In practice, slower dose escalation may be necessary in some participants, and deviations from this protocol (for example escalation by 2.5 mg every two weeks) will be permitted at the clinician’s discretion to bring participants to the maximum tolerated dose as closely in line with the stated strategy as possible.

If participants show toxicity to MTX upon dose escalation the dose will be dropped to the maximum tolerated dose (minimum dose, 7.5 mg/week) and this will be maintained for the duration of the study. In our pilot study of MTX in OA, 20 of the 23 participants completing the study did so on a dose of 15 mg or more. Dose reduction (to 7.5 to 12.5 mg) was required in four participants; one due to renal impairment and three due to side effects (nausea, headache and sore roof of mouth), all of which improved upon dose reduction. Participants who are intolerant of oral MTX will not be switched to subcutaneous MTX (a common practice for RA), due to complexities in maintaining the blind.

All participants will be routinely reminded and encouraged to comply with the prescribed dose of investigational medicinal product (IMP). However, given the long half-life of MTX, those who miss doses of IMP will be allowed to restart medication if they so wish, and will not be handled differently during the course of follow-up. For the purposes of analysis, a participant missing more than four doses of MTX within any three-month period will be counted as a ‘non-complier’.

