#### Concomitant medication

In order to maintain the pragmatic nature of the trial, there are no restrictions written into the protocol with regard to concomitant analgesic medications. All participants, whether on MTX or placebo, will be allowed to continue taking the treatments for knee OA that they are taking at their screening visit for the duration of the trial. Investigators will be responsible for the overall management of a participant’s medication, and will ask participants to avoid changing their analgesic or anti-inflammatory medication for the duration of the trial. However, if a participant is experiencing increased pain and requires an increase in the dose of analgesics then the use of paracetamol, topical or oral NSAIDs or opioids, or a combination of these will be permitted, but the reason for the dose increase and the dose used will be documented. The choice of medications and doses to be used lie with the principal investigator and clinicians working at study sites in order to ensure that treatment for participants in both groups is optimized. Participants will be permitted to continue current use of chondroitin and glucosamine, provided the dose has been stable for three months at study entry; however their use must be clearly documented in the case report form (CRFChondroitin or glucosamine therapy will not be commenced during the duration of the trial. Chronic NSAID and opioid use days in the last three months) will be included as a covariate in the analysis.

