### Primary endpoint analysis

The primary analysis will be conducted on the intention-to-treat population, including all randomized participants in the groups to which they were randomized. A per protocol population (excluding major protocol violations) will be used to check the robustness of the primary analyses. The safety population will consist of all patients receiving at least one dose of the study drug.

The first 30 participants (included in the internal pilot study) will be included in the main trial analysis along with the rest of the participants. Wittes and Brittain show that sample size re-estimation using an internal pilot study has minimum impact on the overall type I error, therefore an alpha level of 0.05 will still be used for the primary analysis [57].

The pilot phase analysis, which will be conducted after primary outcome data becomes available for the thirtieth participant, will include the following:Assessment of the variability of the primary outcome measure, the estimate (SD) will be used to update the sample size calculation;Consent rate (out of the number of information packs sent out during the pilot phase);Retention rates associated with each treatment andReturn rate for the six-month outcome assessment.

The primary analysis for the main study will be conducted using linear regression adjusting for the baseline measure. Treatment groups will be compared at six months with respect to their average overall knee pain severity over the previous week.

All secondary analyses will be conducted using linear or logistic regression, depending on the type of outcome measure, adjusting for the same covariates as the primary analysis. The intention-to-treat population will be used for all secondary analyses. All secondary outcomes will be described descriptively (mean, SD, median, minimum and maximum for continuous data and counts and percentages for categorical data). The Short Form-12 questionnaire will be summarized for all components. To minimise multiple testing, only the overall physical component score and mental component score will be analysed, using the same analysis methods as for the primary outcome. For continuous outcomes the regression model assumptions will be checked and, if necessary, data will be transformed prior to analysis if this improves the model fit, or normalises the distribution of residuals.

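### Allocation is described as 1:1 within each site, but neither the primary model nor the models that inherit its covariates names a site term; the likely cost is a slightly conservative test, not bias

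*Protocol article*

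**What the plan says.** On design, the Methods/Design section states: "The PROMOTE trial is an investigator-initiated, multi-centre, 160 patient, randomized placebo-controlled trial". It does not give the number of sites. The allocation paragraph that follows the Figure 2 legend says "study medication will be packed into bulk numbered bottles according to a randomization schedule", that pharmacies issue the medication in number order, and that "Participants in each site will be randomly assigned to the intervention arm or the placebo arm in a ratio of 1:1". It mentions neither stratification nor blocking.

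On analysis, Primary endpoint analysis states: "The primary analysis for the main study will be conducted using linear regression adjusting for the baseline measure". Secondary outcomes are to be analysed by linear or logistic regression, "adjusting for the same covariates as the primary analysis", and the MRI comparison uses the same covariate set. Site appears in none of these models.

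On covariates, the Concomitant medication section says that days of chronic NSAID and opioid use in the preceding three months "will be included as a covariate in the analysis". Primary endpoint analysis does not repeat this.

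On site practice, Concomitant medication says: "The choice of medications and doses to be used lie with the principal investigator and clinicians working at study sites". The dosing section says that departures from the escalation schedule "will be permitted at the clinician’s discretion to bring participants to the maximum tolerated dose". The final decision on corticosteroids also rests with the local investigator or study physician.

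**The concern.** When allocation is balanced within a factor, the analysis should normally include that factor. Balance removes between-site differences from the treatment contrast. A model without site nevertheless leaves those differences in the residual, so the reported standard error is larger than the true one. The confidence interval is then a little too wide and the P value a little too large.

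Site could plausibly matter here. The primary outcome is self-reported pain, and local clinicians have discretion over escalation, analgesics and steroids. Because the covariate set is inherited, the omission runs through every efficacy model. At stake is some precision in a trial planned on 128 evaluable participants.

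**Working it through.** **Inputs from the Protocol article (Sample size section).** Difference 2 points, SD 4, 80% power, 5% significance (two-sided assumed), 64 per arm, 20% dropout, 160 in total.

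**Assumed inputs.** The ICC, meaning the share of outcome variance that lies between sites, is varied from 0 to 0.10. The number of sites is set at 8 or 15 in the simulation. The article gives neither.

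**Step 1: the plan's own figure.** Normal approximation: n per arm = 2 × (1.960 + 0.842)² × 4² / 2² = 62.8, so 63. The t-based calculation gives 64, with power 80.1%. Then 128 / 0.8 = 160. The stated sample size reproduces.

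**Step 2: standard error.** With exact balance within site, the true SE of the treatment difference uses SD 4 × √(1 − ICC), while the model without site reports an SE based on SD 4. The ratio of reported to true SE is 1/√(1 − ICC): 1.010 at ICC 0.02, 1.026 at 0.05 and 1.054 at 0.10.

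**Step 3: type I error and power at 64 per arm.** The reported SE is 4 × √(2/64) = 0.707.
- Actual alpha without site = 2 × [1 − Φ(1.96/√(1 − ICC))].
- Power without site = Φ[(2 − 1.96 × 0.707) / (0.707 × √(1 − ICC))].
- Power with site = Φ[2 / (0.707 × √(1 − ICC)) − 1.96].

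| Assumed ICC | Actual alpha, no site term | Power, no site term | Power, site term |
|---|---|---|---|
| 0 | 5.0% | 80.7% | 80.7% |
| 0.01 | 4.9% | 80.9% | 81.1% |
| 0.02 | 4.8% | 81.0% | 81.5% |
| 0.05 | 4.4% | 81.4% | 82.7% |
| 0.10 | 3.9% | 82.0% | 84.7% |

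The power forgone is 0 at ICC 0, about 0.5 points at 0.02 and about 2.7 points at 0.10.

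**Step 4: simulation.** 128 participants in equal or near-equal sites, permuted blocks of four within site, site as fixed effects, 8,000 runs per setting.

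| Sites | ICC | Alpha without / with site | Power without / with site |
|---|---|---|---|
| 8 | 0 | 5.0% / 4.9% | 80.2% / 80.1% |
| 8 | 0.10 | 4.3% / 5.4% | 82.5% / 85.0% |
| 15 | 0 | 5.1% / 5.2% | 79.9% / 79.4% |
| 15 | 0.10 | 4.0% / 5.1% | 82.0% / 84.1% |

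The simulation agrees with the formulas in direction and size. It also shows the price of the site term when sites do not differ: about 0.5 points of power with 15 small sites.

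**The case against.** **The details may be in the SAP.** The Statistical analysis section leaves full methods to a statistical analysis plan that is not available here, and that plan may add site. This stands in part. However, the article does not leave the primary model open: it names the method and the adjustment. A site term added later would change a published primary model, so it should be settled before any data are seen.

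**Balance by site is inferred.** This stands. The wording points to a 1:1 ratio within sites, but an unstratified 1:1 schedule would also fit the text. A reader might infer that the design guarantees balance and that the analysis throws it away. The article does not establish the first, and the second is too strong: any balance still protects the estimate from site differences even if site is left out of the model.

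**There is no bias on either reading.** This also stands. A reader might infer that leaving site out lets site differences distort the comparison. Under balanced allocation they cancel. Under unstratified allocation any imbalance is due to chance, and the ordinary standard error already allows for it.

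**The adjustment is not for baseline pain alone.** Correct. Concomitant medication adds NSAID and opioid use days, so the covariate list in Primary endpoint analysis is visibly incomplete. That weakens any inference from its silence on site, but it is itself an inconsistency to resolve.

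**The effect is small and site variation is not shown.** Clinician discretion makes between-site differences plausible but does not demonstrate them. Dropout would also erode exact balance, and with it the gain calculated above. The planned 80% power is met without a site term, and the SD of 4 is described as conservative beside cited within-group SDs of 2.1 and 2.4. At SD 2.4 the SE is 2.4 × √(2/64) = 0.424, and power is Φ(2/0.424 − 1.96), above 99%.

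**Conclusion.** The point holds as a modest one. Allocation is described as 1:1 in each site, and the stated primary model, with the secondary and MRI models that follow it, has no site term. If allocation is balanced by site, the result is a reported standard error about 1% to 5.4% too large for an ICC of 0.02 to 0.10. Over an ICC of 0 to 0.10, actual alpha runs from 5.0% down to 3.9%, and 0 to about 2.7 points of power are forgone. The error is in the conservative direction. These figures rest on assumed ICCs and on close to exact balance within sites.

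The documents do not support a claim of bias, of inflated type I error or of an inadequate sample size. The mismatch between the Concomitant medication and Primary endpoint analysis sections over the NSAID and opioid covariate does not depend on any of these assumptions.

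**What to change.** 1. State whether the randomization schedule is stratified or blocked by site.
2. Include site in the primary, secondary and MRI models. Choose a random intercept or fixed effects once the number of sites is known: many small sites favour a random intercept, whereas with few sites its variance may be poorly estimated and fixed effects are reasonable.
3. Give one covariate list for the primary analysis that agrees with the NSAID and opioid covariate in Concomitant medication, and settle it before data are analysed.

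The cost is one model term, using information already held for every participant. If outcomes do not differ between sites and there are many small ones, it costs about 0.5 points of power. The recruitment target of 160 does not change.
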